## Abstract

**Introduction:**

Osteoarthritis (OA) pain is a major cause of long-term disability and chronic pain in the adult population. One in five patients does not receive satisfactory pain relief, which reflects the complexity of chronic pain and the current lack of understanding of mechanisms of chronic pain. Recently, duloxetine has demonstrated clinically relevant pain relief, but only in half of treated patients with OA. Here, the aim is to investigate the neural mechanisms of pain relief and neural signatures that may predict treatment response to duloxetine in chronic knee OA pain.

**Methods and analysis:**

This is an ongoing single-centre randomised placebo-controlled mechanistic study (2:1 (placebo) allocation), using a multimodal neuroimaging approach, together with psychophysiological (quantitative sensory testing), genetics and questionnaire assessments. Eighty-one subjects with chronic knee OA pain are planned to power for between-group comparisons (placebo, duloxetine responder and duloxetine non-responder). Participants have a baseline assessment and, following 6 weeks of duloxetine (30 mg for 2 weeks, then 60 mg for 4 weeks), a follow-up evaluation. Brain imaging is performed at 3T with blood-oxygen-level dependent functional MRI at rest and during pin-prick nociceptive stimulation for main outcome assessment; arterial spin labelling and structural imaging (T1-weighted) for secondary outcome assessment. Questionnaires evaluate pain, negative affect, quality of sleep and cognition.

**Ethics and dissemination:**

The study has been approved by the East Midlands, Nottingham and is being carried out under the principles of the Declaration of Helsinki (64th, 2013) and Good Clinical Practice standards. Results will be disseminated in peer-reviewed journals and at scientific conferences.

**Trial registration number:**

This trial is registered at ClinicalTrials.gov (NCT02208778).

This work was supported by Arthritis Research UK (Grant 18769).

Strengths and limitations of the studyThis study attempts to shed light on the little understood mechanisms of pain relief in chronic pain.By undertaking an innovative and integrative approach, which combines multimodal neuroimaging, quantitative sensory testing and psychometric questionnaire assessments, drug effects and predictors of treatment response to duloxetine are aimed to be identified.A crossover design would have ideally been employed. However, a parallel design was chosen to minimise dropout rates.

## Background and rationale

Osteoarthritis (OA) is a major cause of long-term disability and chronic pain in the adult population. Knee and hip OA combined ranked 11th in a recent survey of global burden of disease, and symptomatic knee OA is several folds more common than hip OA.^1^ Current treatment options consist of a combination of pharmacological and non-pharmacological alternatives.^2^ Despite these options, around 20% of patients do not get satisfactory pain relief, even after undergoing joint replacement surgery.^3^ This strongly supports the notion that chronic osteoarthritis pain has a strong central component.^4–6^

Application of advanced neuroimaging tools led to novel understanding of central mechanisms underpinning acute and chronic pain states.^7^ Functional imaging in particular lends itself to the mechanistic study of analgesic treatment.^5 8–10^ Neuroimaging may also prove useful in guiding mechanism-based personalised therapy.^10–12^

To comprehensively describe brain activation states across regions and functional properties, the concept of so-called brain ‘signatures’ has emerged that can be derived from regional and network analysis of blood-oxygen-level dependent (BOLD) functional MRI data at rest or during controlled stimulation, or from cerebral blood flow maps based on arterial spin labelling (ASL) techniques.^13 14^

Duloxetine, a serotonin and norepinephrine reuptake inhibitor, has antidepressant and anxiolytic properties and is currently also used to treat chronic pain conditions. However, the precise mechanisms by which this drug acts to relieve pain are unclear and only around 50% of patients with OA have sufficient pain relief after duloxetine intake^15^; currently there is no way to predict responders.^15 16^ In healthy participants, duloxetine was found to attenuate activity in affect processing areas (amygdala, thalamus, insula and anterior cingulate cortex) while simultaneously increasing functional coupling between the amygdala and the anterior insula during an emotional face matching task.^17^ Duloxetine in major depression augmented connectivity in the anterior default mode network,^18^ while reduced connectivity within the subgenual cingulate was predictive of clinical antidepressant response.^18^

The aim of this study is to investigate the neural mechanisms of pain relief in chronic OA pain following treatment with duloxetine and to establish multimodal brain signatures to predict treatment response. We will use a unique multimodal MRI design to identify key mechanisms and predictors of duloxetine-induced pain relief in chronic OA pain. This will include brain resting state functional connectivity, ASL, nociceptive functional (f)MRI, structural T1-weighted brain MRI, proton spectroscopy, quantitative sensory testing (QST) and questionnaire assessments.

We hypothesise that responding and non-responding patients with OA have different limbic signatures, differences in negative affect and sensory pain phenotypes. Additionally, we hypothesise that duloxetine induces functional brain changes in emotional regulatory networks.

## Primary objectives

The objective of this study is to identify a functional change in brain signature indexing the analgesic mechanism of duloxetine and to identify brain imaging and psychophysical markers that predict the response to duloxetine treatment.

## Main hypotheses

Analgesic response to duloxetine treatment can be predicted using a range of baseline brain imaging markers and QST.Analgesic response to duloxetine is mediated by modulation of neural networks underpinning emotional control.Duloxetine-induced changes in brain activation differ between responders and non-responders.

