**Figure 1 F1:**
[figure not shown]
Participation timeline and general characteristics of each study visit. QST, quantitative sensory testing.

Participants are assigned, by the investigators, a unique identification number (sequentially numbered) and attend the university twice, for both a baseline and follow-up visits. Treatment consists of 6 weeks of taking either duloxetine capsules or placebo equivalent, followed by 2 weeks of dose reduction for those taking duloxetine to minimise drug withdrawal effects (figure 1). To minimise potential side effects, participants take one tablet (duloxetine 30 mg) daily during 2 weeks prior to switching to the target dose of 60 mg/day. Both researchers and participants are blinded to the treatment allocation until data acquisition is complete. At the end of the follow-up visit, individual allocation is disclosed to the participant only by one of the CTP staff members who are not involved in the any data analysis or research procedures. Data analysts will be blinded to treatment allocation.

Individual participation in the study is for around 8 weeks, starting with signing informed consent and ending with the conclusion of the drug reduction phase.

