### Experimental testing

The experimental testing is primarily based on multimodal neuroimaging and QST, in conjunction with questionnaire assessment and genetics. This should provide a broad evaluation of the multifaceted nature of pain, assessing both central and peripheral mechanisms, as well as psychological and cognitive traits, among others, which should allow pinpointing precise phenotyping of patients into distinct groups. Time points and types of data being collected are summarised in figure 2 and details of questionnaires are given below.

Questionnaires:PainDetect (baseline)—a screening questionnaire to identify neuropathic components of pain.^19^
Pain Catastrophizing Scale (PCS) (baseline)—a 13-item scale to measure pain catastrophising, which can be split into three subscales named rumination, magnification and helplessness.^20^
State-Trait Anxiety Inventory (STAI) (baseline)—a psychological inventory assessing anxiety. It contains 40 items and can be split into two subscales being state anxiety and trait anxiety.^21^
Beck Depression Inventory II (BDI) (baseline)—a 21-item multiple-choice self-report scale for measuring the severity of depression.^22^
The intermittent and constant pain score (ICOAP) (baseline and follow-up)—an 11-question scale to characterise pain in individuals with osteoarthritis pain. It gives two subscales relating to intermittent and constant experience of pain.^23^
The Pain Sleep Questionnaire (baseline)—a five-item tool to assess the impact of pain on sleep.^24^
Brief Pain Inventory (BPI) (daily)—a nine-item questionnaire for measuring the severity of pain and the impact of this pain on daily functioning. The severity subscale is used to define the response definition (below).^25^
Mini-Cog (baseline)—contains a three-item recall test and a clock drawing test to screen cognitive impairment.^26^
Educational level (baseline).Questions on belief (baseline)—consist of four questions to assess an individual’s expectations on treatment and medical care.^27^

Participant general details:Age.Sex.Pain intensity (measured on a numeric rating scale ranging from 0 to 100, where 0 represents no pain at all and 100 stands for excruciating pain).Pain duration.Analgesia intake (last 24 hours).Caffeine intake (last 24 hours).Average daily caffeine intake.Average weekly alcohol intake.Medication.

Other:10 mL blood samples.Analgesia diary (daily).

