### Response definition

Response to duloxetine is defined as a 50% reduction in the severity of ongoing pain from baseline to end of treatment, as measured by the BPI severity subscale. This threshold was chosen based on previous randomised controlled trials of duloxetine in osteoarthritis.

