### Primary outcomes

#### Treatment mechanism

Change in the regional response of BOLD contrast to pinprick nociceptive stimulation after duloxetine treatment (MRI2) versus baseline (MRI1) in treatment responder group.Functional connectivity change from baseline (MRI1) to post duloxetine treatment (MRI2) using network metrics of BOLD fMRI under resting condition in treatment responder group.

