#### Secondary outcomes

Difference in the regional response of BOLD contrast to pinprick nociceptive stimulation after duloxetine treatment (MRI2) between responder and non-responder groups.Functional connectivity differences post duloxetine treatment (MRI2) using network metrics of BOLD fMRI under resting condition between treatment responder and non-responder groups.Correlation between baseline CPM and TS with brain activity and connectivity changes from baseline to post 6 weeks of duloxetine treatment (rsfMRI and pinprick fMRI).Group differences in brain activity (pinprick fMRI and rsfMRI) and structure (T1-weighted brain MRI) in pain processing, limbic and modulatory pathways changes from baseline to following 6 weeks of duloxetine treatment, in comparison to placebo.Identification of baseline QST (CPM, TS, PPT) and questionnaire parameters (BDI, STAI, PCS, ICOAP) that predict response to duloxetine.Multivariate treatment response prediction model.

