### Data analysis

Clinical, QST and psychometric data will be compared between groups and conditions using the latest versions of statistical and image analysis software including SPSS (version 21.0).

Brain imaging data will be analysed using the latest versions of several established toolboxes: FSL (FMRIB Software Library),^28^ PyMVPA (Multivariate Pattern Analysis),^29^ Statistical Parametric Mapping V.8 (London, UK), REST (Resting-State fMRI Data Analysis Toolkit), Brain Connectivity Toolbox and GRETNA (Graph Theoretical Network Analysis)^30–32^ and LCModel (Linear Combination Model) for MRS data.^33^ All data will undergo established quality control and standard recommended preprocessing. Preprocessing steps for functional data include motion correction, slice-timing correction using Fourier-space time-series phase-shifting, non-brain tissue removal, spatial coregistration to T1-weighted image and normalisation to the MNI anatomical standard space. Spatial smoothing will be carried out using an isotropic Gaussian kernel and a high-pass temporal filtering will be applied. Next, for task-related fMRI, statistical maps will be generated for contrasts of interest, such as to identify brain activity evoked by pinprick in each individual scan using first-level general linear model.

Z-scores will be extracted from regions of interest of pain processing nodes defined from meta-analysis,^7^ emotion regulatory, default mode and salience network including anterior cingulate cortex, anterior insula, amygdala, brain stem and thalamus for both task-related and resting functional maps. Individual functional connectivity maps will be also generated. These will be used on higher level analysis which will include, among others: (1) Paired t-test to evaluate treatment effects; (2) two-sample t-test to compare groups (responders and non-responders) at baseline; (3) correlation analysis to determine associations with psychometric and QST measurements.

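### Main hypothesis 2 claims mediation, but a single end-of-treatment scan and responder-based outcomes can show only association between network change and pain relief

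*Protocol article*

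**What the plan says.** Main hypotheses: "Analgesic response to duloxetine is mediated by modulation of neural networks underpinning emotional control". Primary objectives also makes the analgesic mechanism of duloxetine a target of the study.

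Timing (text below Figure 1, and Response definition): participants "attend the university twice, for both a baseline and follow-up visits", so there is one scan before treatment and one after six weeks of it. Response is "defined as a 50% reduction in the severity of ongoing pain from baseline to end of treatment" on the BPI severity subscale. Pain itself is recorded more often (Experimental testing): "Brief Pain Inventory (BPI) (daily").

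Primary outcomes, Treatment mechanism: one outcome is the change in pinprick BOLD response in responders. The other is "Functional connectivity change from baseline (MRI1) to post duloxetine treatment (MRI2) using network metrics of BOLD fMRI under resting condition in treatment responder group".

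Secondary outcomes: the pinprick response is compared "after duloxetine treatment (MRI2) between responder and non-responder groups", and the resting-state counterpart is "Functional connectivity differences post duloxetine treatment (MRI2) using network metrics of BOLD fMRI under resting condition between treatment responder and non-responder groups". A further item compares brain change with placebo, and another correlates brain change with baseline CPM and TS. Other outcomes adds GABA modulation in relation to change in pain severity, as exploratory.

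Data analysis: an open list of higher-level analyses names paired t-tests, two-sample t-tests of responders and non-responders at baseline, and "correlation analysis to determine associations with psychometric and QST measurements".

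**The concern.** A mediation claim has two links: drug to network change, and network change to pain change given the drug. It also has a direction: the network must move first. The outcomes address the first link through the placebo comparison. They address the second only by splitting participants on whether pain fell by half, and nothing in the schedule addresses direction.

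Followed as written, the trial could report that emotional-control networks changed in people selected because their pain fell, and this could be read as support for hypothesis 2. The same finding would appear if those networks simply track current pain, whatever lowered it.

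**Working it through.** **1. The plan's own figure.** Sample size estimation gives 19 usable per group. Then 19/0.9 = 21.1, so 22; 19/0.9/0.8 = 26.4, so 27; 27 × 3 = 81. The significance level is 0.05/10 = 0.005. These reproduce and are not at issue. They supply 2 × 19 = 38 usable duloxetine participants for step 4.

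**2. Links against outcomes.**
- Drug to network: brain change compared with placebo (secondary).
- Network to pain, given drug: responders against non-responders at MRI2 (secondary; post-treatment level, pain in two classes), and GABA against pain change (exploratory). No listed outcome relates change in an emotional-control network to the amount of pain change.
- Order: no scan lies between baseline and end of treatment. Daily BPI dates the fall in pain, but nothing dates the change in the brain.

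**3. Can one concurrent reading tell the directions apart?** Let x be arm, M network change and Y pain reduction. The paths are assumed for illustration.

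*Mediator:* M = 0.8x + error (variance 1); Y = 0.3x + 0.5M + error (variance 1).
- Arm effect on M is 0.8; on Y it is 0.3 + 0.5 × 0.8 = 0.7.
- Within arm: var M = 1, var Y = 0.25 + 1 = 1.25, covariance = 0.5.

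*Consequence:* Y = 0.7x + error (variance 1.25); M = 0.52x + 0.4Y + error (variance 0.8).
- Arm effect on Y is 0.7; on M it is 0.52 + 0.4 × 0.7 = 0.8.
- Within arm: var Y = 1.25, var M = 0.16 × 1.25 + 0.8 = 1, covariance = 0.4 × 1.25 = 0.5.

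Every mean, variance and covariance agrees. The fitted indirect effect is 0.8 × 0.5 = 0.40 in both, and the within-duloxetine correlation is 0.5/√1.25 = 0.447. A simulation of 400,000 subjects allocated 2:1 gave 0.399 and 0.445 for the mediator, and 0.398 and 0.448 for the consequence.

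Now remove the drug's direct path to the brain (0.52), so that the network only reacts to pain:
- Arm effect on M is 0.4 × 0.7 = 0.28 and the slope of Y on M stays 0.5. The fitted indirect effect is 0.28 × 0.5 = 0.14, although nothing is mediated.
- If responders are the upper half of the duloxetine arm, their mean Y lies √(2/π) × √1.25 = 0.798 × 1.118 = 0.892 above the arm mean. Their mean network change is 0.28 + 0.4 × 0.892 = 0.64 within-arm SD. The responder-only primary outcome would be clearly positive.

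**4. Cost of the responder split.** Assumptions: correlation r = 0.5 between network change and pain change, bivariate normal; half of the duloxetine arm respond (as the protocol expects); 19 per group; two-sided 0.05; the group contrast taken on brain change.
- Split: standardised difference d = 2r√(2/π)/√(1 − 2r²/π) = 0.798/0.917 = 0.87. Noncentrality is 0.87 × √(19 × 19/38) = 2.68 on 36 df, giving power of about 74%. Simulation gives about 73%.
- Continuous: atanh(0.5) × √35 = 0.549 × 5.916 = 3.25; 3.25 − 1.96 = 1.29, giving about 90%.
- The same formulas give 32% against 45% at r = 0.3, 52% against 71% at r = 0.4, and 90% against 98% at r = 0.6.

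**The case against.** The plan does more than a quick reading suggests, and several stronger charges fail.
- A reader might infer that pain is read only once after treatment. It is not: BPI is daily and ICOAP is taken at baseline and follow-up. The single reading applies to the scan and to the response definition.
- A reader might infer that no outcome connects brain to pain. The responder comparisons at MRI2 do so within the treated arm, main hypothesis 3 concerns responder differences in brain change, and the GABA outcome uses change in pain severity.
- A reader might infer that no mediation model is planned. The analysis list is expressly open, and a full protocol or SAP may hold one. Its absence from a condensed article is not an error.
- A reader might infer that mechanism rests on a correlation among 19 responders and is badly underpowered. No such correlation is planned; the relevant comparison is the one in step 4.

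It is also fair to say that no listed outcome itself claims mediation, and that an added regression model cannot recover direction. Step 3 shows the latter.

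All of this stands, and it narrows the point. It does not remove it. The wording of hypothesis 2, the responder-only primary outcomes and the two-scan schedule are fixed in this document, and no later analysis can supply an order in time that was not observed.

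**Conclusion.** Hypothesis 2 claims more than the design can test. The trial can show that network change and pain relief go together. It cannot show that the first produced the second, and the responder-only primary outcomes would look favourable either way.

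The conclusion about direction rests on the visit schedule. The 0.40 in both models illustrates it under assumed paths. If the effect ran wholly through one route, the two directions would leave different patterns in principle, but the protocol does not assume this. Network change is also not randomised, so common causes of brain and pain change remain possible.

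The power loss from dichotomising, roughly 73% against 90%, depends on the assumed r = 0.5. It is about 13 to 19 points for r from 0.3 to 0.5 and about 8 at r = 0.6. This is a worthwhile, inexpensive improvement to the claim and the analysis. It does not invalidate the study.

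**What to change.** 1. Restate hypothesis 2 so that analgesic response is 'associated with' modulation of emotional-control networks. State that a positive result is consistent with mediation, not proof of it.
2. Add to the mechanism outcomes an analysis in all participants of both arms who have MRI1 and MRI2: (a) change in one prespecified emotional-control measure on randomised arm; (b) change in BPI severity, kept continuous and using the same baseline and end-of-treatment values as the response definition, on change in that measure, with arm and both baselines in the model. State that this model does not establish time order.

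Cost: a weaker stated claim, one extra model on data already collected, and the need to choose the measure in advance from the regions and networks in Data analysis. No visit, scan or participant is added.

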## Design and methods

This is a single-centre, double-blind, placebo-controlled mechanistic study being conducted at the University of Nottingham (UK).

### Inclusion criteria

To participate in this study, individuals must have chronic knee pain with radiographically defined OA changes (Kellgren Lawrence grade 2 or higher), be able to consent to participation and be aged 35 or older. They must also be free of major medical, neurological and psychiatric comorbidities known to affect neural processing of pain.

### Exclusion criteria

Potential candidates meeting any of the criteria listed below are excluded from participation.

General:Significant medical conditions, including uncontrolled hypertension, insulin-dependent diabetes, dementia, Parkinson’s disease, epilepsy, multiple sclerosis, active cancer, major depressive disorder, mania, bipolar and schizophrenia. This is judged by a qualified physician based on medical records.Refusal by candidate to GP being informed.Planned total knee replacement.

MRI related:Intraocular metallic foreign bodies.Intracranial aneurysm clips.Cardiac pacemakers and defibrillators.Cochlear implants.Significant head tremor.Potential metal foreign bodies due to previous accidents.Breastfeeding or pregnancy, confirmed by pregnancy test.Unfitness for the MRI scanner, according to the judgement of medically qualified personnel, either on the research team or the patient’s clinical team (eg, due to back pain, claustrophobia, acute sickness, etc). This includes patients with signs of impaired temperature regulation such as an extremely high fever.Patients with large tattoos, specifically in the head, neck or shoulder region.Metallic agents embedded within the body (ie, Shrapnel, surgical pins).

Duloxetine related:Uncontrolled narrow-angle glaucoma.Recent usage of monoamine oxidase inhibitor or Mellaril (thioridazine).Taking St John’s Wort (Hypericum perforatum).On fluvoxamine, ciprofloxacin or enoxacin.Taking other medicines containing duloxetine.Liver disease.Renal impairment.Currently on antidepressant treatment, including treatment for pain with tricyclic agents such as amitriptyline.Taking tramadol.Known hypersensitivity, allergy or intolerance to one of duloxetine's components.Unwillingness to take caution in relation to use of other centrally active substances such as alcohol and sedative drugs.Current treatment with potent inhibitors of CYP1A2 like fluvoxamine.History of seizures or any drug lowering the seizure threshold.

